## Abstract

**Background:**

The Mediterranean diet (MD), globally recognized for its sustainability and health benefits, traditionally emphasizes the consumption of plant-based foods in raw or minimally processed forms. However, shifting lifestyles, even in Mediterranean regions, have led to an increasing consumption of ultra-processed foods (UPF). Epidemiological evidence suggests that UPF consumption may be detrimental to human health, but there is only one clinical trial on this topic which is largely debated in the scientific community. This study aims to investigate the impact of the inclusion of UPF within a Mediterranean-based dietary pattern on cardiometabolic markers, gut microbiota, and other markers of human and planet health.

**Methods:**

Fifty clinically healthy individuals showing overweight and presenting a low-to-moderate cardiovascular risk profile will be recruited for a 7-month randomized, open, cross-over dietary trial. Eligible participants will be randomly assigned to a 3-month high-UPF MD (intervention group) or a low-UPF MD (control group), with a 1-month wash-out period. Both intervention diets will have identical food group compositions, with the intervention group consuming 5 servings/day of selected UPF items, and the control group consuming raw/minimally processed items from the same food group. Blood, urine, and fecal samples, alongside food/lifestyle diaries, will be collected from each participant before and after the dietary interventions. The primary endpoint will be the change in plasma LDL-cholesterol levels from baseline. Additional markers include blood pressure, anthropometric parameters, chemical parameters, glucose and lipid-related metabolic markers, incretins, inflammatory and oxidative stress markers, fecal microbiota composition, and short-chain fatty acids. Finally, food waste production will be evaluated through specific validated food diaries. The study has been approved by the Ethical Committee of the University of Milan and the Tuscany Regional Ethics Committee of the Azienda Ospedaliera Universitaria (AOU) - Careggi, Florence.

**Discussion:**

Results from the PROMENADE study will improve knowledge about the impact of UPF consumption on human and planet health and will contribute to the scientific debate on this topic.

**Trial registration:**

ClinicalTrials.gov NCT06314932. Registered on March 13, 2024.

**Supplementary Information:**

The online version contains supplementary material available at 10.1186/s13063-024-08470-6.

### Introduction

#### Background and rationale {6a}

The Mediterranean diet (MD) is a dietary pattern based on the traditional foods eaten in the countries overlooking the Mediterranean Sea, characterized by a substantial intake of plant-based foods and moderate consumption of animal-based products. In recent decades, the MD has emerged as one of the healthiest dietary choices, as for human and planet health [1]. Its increased adherence has demonstrated robust associations with an enhanced cardiometabolic risk profile, reduced risks of major chronic diseases (such as cardiovascular disease, diabetes, and cancer), and a noteworthy decrease in overall mortality [2, 3]. Moreover, the MD is recognized for its low environmental impact, biodiversity richness, high sociocultural food values, and positive local economic contributions [4]. Consequently, the MD has earned its place among the most sustainable diets, aligning with the imperative to shift toward more sustainable food systems and dietary patterns, as emphasized in the “Farm to Fork Strategy” [5].

Despite the considerable evidence supporting the MD, shifts in lifestyle and available time for food preparation are impacting adherence [6]. In this context, freshly prepared meals and dishes, which are the basis of traditional dietary patterns recognized to promote long and healthy lives such as MD, are increasingly replaced by ultra-processed foods (UPF). Defined within the NOVA classification as formulations derived from industrial processes, UPF encompasses products like breakfast cereals with added sugars, savory snacks, reconstituted meat products, and pre-packaged frozen dishes [7]. The global increase in UPF consumption is alarming, with reports indicating that UPF can contribute to 50–60% of the total diet in the USA, Canada, and the UK. Although Italy currently maintains a lower energy intake from UPF (approximately 10%), significant variations based on sex, age, and body mass index (BMI) have emerged, with higher consumption among overweight and obese individuals [8]. High UPF intake correlates with diets high in calories, free sugars, fat, and saturated fats, coupled with low dietary fiber [9]—a combination associated with an increased risk of cardiometabolic diseases, cerebrovascular diseases, depression, and all-cause mortality [10].

The underlying mechanisms linking UPF to adverse health effects are subjects of ongoing debate and hypothesis formulation. UPF, seemingly indicative of poor food quality, exhibit higher levels of saturated fats, added sugars, sodium, lower vitamin and fiber content, and greater energy density compared to unprocessed or minimally processed foods [9]. Alternative explanations include the presence of adverse compounds formed during industrial food processing, increased exposure to endocrine-disrupting chemicals and phthalates from industrial plastic packaging, and sensory properties contributing to delayed satiety signaling and accelerated eating rates [11–13]. Recently, there is a hypothesis suggesting that UPF may adversely impact health by modifying the gut microbiome, influencing the selection of microbes associated with inflammation-related diseases, such as cardiovascular and metabolic diseases [14].

Despite these hypotheses and the growing epidemiological evidence indicating potential harm from UPF consumption, only one clinical trial has been published thus far [15]. Hall and colleagues conducted a randomized controlled trial involving 20 adults randomized to receive either UPF or unprocessed ad libitum diets for 2 weeks. The study reported a significant increase in body weight and overall energy intake only after the UPF-rich diet. However, limitations related to the trial’s short duration and dietary intervention composition have been highlighted [16]. Furthermore, the study primarily focused on energy intake, overlooking other potential mechanisms, especially those mediated by modulation of the microbiota. Hence, the need persists for additional randomized controlled trials to delve deeper into the factors associated with the relationship between UPF consumption and human health markers, aiming to elucidate potential mechanisms. Additionally, investigating the effect of UPFs within overall healthy and balanced dietary patterns to consider the impact of the “overall diet” remains an intriguing avenue to explore.

## Objectives {7}

The PROMENADE study aims to assess whether the inclusion of UPF within a Mediterranean-based dietary pattern affects both human health and environmental markers in a group of overweight Italian subjects through a randomized, controlled, crossover trial, comparing the effects of two identical MD interventions in terms of calorie content and nutritional balance but differing in the degree of UPF consumption.

## Trial design {8}

A 7-month randomized, cross-over, two-arm, open-label, superiority trial with a 1:1 allocation ratio to either intervention or control arms will be conducted, adhering to the SPIRIT reporting guidelines (see Fig. 1 and Supplementary file 1). In the development of the study protocol, there was no direct involvement from the public or patients. Despite the acknowledged significance of patient and public engagement in research, the protocol for this study was formulated within the framework of scientific and clinical expertise.

**Fig. 1 Fig1:**
[figure not shown]
SPIRIT figure reporting the phases of the trial and data collection time points

## Methods: participants, interventions, and outcomes

### Study setting {9}

The study will be conducted by three research units (RUs): University of Milan (RU1), University of Florence (RU2), and University of Teramo (RU3). Participant recruitment and clinical evaluations will exclusively take place at RU1 and RU2. For RU1, assessments will be conducted by healthcare personnel at the licensed facility CRC-ICANS, Milan, while for RU2, evaluations will be carried out at the Unit of Clinical Nutrition of the Careggi University Hospital, Florence, Italy.

### Eligibility criteria {10}

Participants meeting the following criteria will be eligible: age > 18 years; BMI between 25.0 and 29.9 kg/m^2^, and the simultaneous presence of at least one of the following criteria, as defined by the guidelines for cardiovascular disease prevention of the European Society of Cardiology: total cholesterol levels > 190 mg/dL; LDL-cholesterol levels > 115 mg/dL; triglyceride levels > 150 mg/dL; glucose levels in the range > 111–125 mg/dL [17].

Participants will be excluded if they do not meet any of the following criteria: the presence of current serious illness or unstable conditions requiring physician supervision of diet (e.g., recent myocardial infarction, chronic liver disease, inflammatory bowel diseases, renal or digestive disorders, diabetes); pregnancy or intention to become pregnant in the next 12 months; lactation; current or recent (past 3 months) use of supplements or antibiotic therapy; current or recent (past 6 months) adoption of specific restrictive diets (e.g., low-calorie or vegetarian diets).

### Who will take informed consent? {26a}

Informed consent will be obtained by trained research personnel, including members of the study team from RU1 and RU2. These individuals will be responsible for clearly communicating the study’s objectives, procedures, potential risks, and benefits to prospective participants. Prior to enrollment, participants will have the opportunity to ask questions and receive detailed information about the trial.

### Additional consent provisions for collection and use of participant data and biological specimens {26b}

Study participants will also be asked for written informed consent to keep the biological samples for future research and to publish the data anonymously.

## Interventions

### Explanation for the choice of comparators {6b}

Our approach to comparators involves implementing two normocaloric diets with identical food group compositions, differing only in the NOVA category of 5 serving/day of foods. This design aims to investigate the impact of UPF within overall healthy and balanced dietary patterns, considering the holistic influence of the “overall diet.” The rationale behind this choice stems from an effort to address the limitations of the sole available randomized controlled trial [15]. Notably, this trial, comparing UPF with unprocessed ad libitum diets over a 2-week period, introduces potential variability in caloric intake and nutritional quality between the groups, thereby introducing confounding factors [16].

### Intervention description {11a}

The intervention group (high-UPF MD group) will consume 5 servings per day of UPF (classified by the NOVA system as NOVA 4) more than the control group. Examples include flavored yogurt, breakfast cereals with added sugar, and processed meat. In the control group, these foods will be substituted with non-ultra-processed alternatives from the same food groups (e.g., plain yogurt, breakfast cereals with no added sugar, unprocessed meat). Diets will be normalized for energy intake based on participant requirements, ensuring complete isocaloric equivalence—approximately 50–55% of energy from carbohydrates, 30–35% from total fat, and 15–20% from protein.

All participants will receive a detailed 1-week menu plan and a leaflet, developed by trial personnel considering diverse factors: (i) alignment with MD pillars and food groups [18]; (ii) adherence to Italian food habits (e.g., five meals per day, a typical sweet-oriented breakfast); (iii) market availability of food pairs within the same group but of different NOVA categories (e.g., NOVA 1 versus NOVA 4). Examples include cereal-based products (e.g., 100% cereal flakes versus cereals with added ingredients, raw pasta versus ready to eat/cook pasta), fruit and vegetables (e.g., minestrone soup made with fresh vegetables versus the canned ones), dairy (e.g., plain versus flavored yogurt), fish (e.g., fillets versus nuggets), and meat products (e.g., steaks versus cured-processed meats).

No meals or supplements will be provided. Participants will prepare their own meals or eat at a restaurant. For both diets, alcoholic beverages will be limited to one per day for women and two per day for men. Participants will be asked not to change their exercise habits during the study.

### Criteria for discontinuing or modifying allocated interventions {11b}

Participants may discontinue the intervention or withdraw from the study under the following circumstances: (1) participant’s request; (2) if the investigator determines that a participant’s health is at risk due to adverse events or the development of concomitant illness post-entry into the study.

### Strategies to improve adherence to interventions {11c}

To improve adherence to the intervention protocols, participants will receive detailed 1-week menu plans from qualified nutritionists, specifying food ingredients by weight and/or volume. Additionally, a comprehensive handout detailing the assigned diet, including possible substitutions, will be provided. We will implement recurring telephonic follow-ups to ensure ongoing support and monitor adherence to the intervention. During these follow-up sessions, participants will have the opportunity to discuss their adherence to the intervention, address any challenges encountered, and provide feedback on their dietary choices and preferences.

### Relevant concomitant care permitted or prohibited during the trial {11d}

During the trial, participants will be requested to advise if they require initiation of cortisone therapies, antidiabetic drugs, or vitamin/mineral supplements, and their continuation in the study will be evaluated accordingly. Additionally, the use of products designed for weight loss will not be permitted. If a participant requires the initiation of any of these products based on a doctor’s recommendation during the intervention period, they will be excluded from the study.

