### Sample size {14}

Sample size calculation is based on the results of a previously published study evaluating the impact of a MD intervention on human health [19]. To detect a 10% change in LDL-cholesterol levels with a statistical power of 90% (beta) and alpha set at 0.05, a randomization of 38 subjects (≥ 19 subjects in each group) is considered necessary. Considering possible dropouts, the number of participants was increased to 25 per group. Dropouts will be incorporated into the intention-to-treat analysis, including all participants initially randomized. In addition, per-protocol analysis will be conducted, focusing on those who successfully complete the study without major deviations.

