### Methods in analysis to handle protocol non-adherence and any statistical methods to handle missing data {20c}

Before starting the data analysis, the level and possible causes of missing data will be investigated using appropriate tables. This information will be used to determine whether the level and type of missing data have the potential to introduce bias into analysis results or substantially reduce the precision of the estimates for the proposed statistical methods. Sensitivity analyses will be performed, based on the assumption that the missing outcomes are the worst or best possible in the different randomization groups. If these show that the conclusions may differ based on the missing values, further multiple imputation will be performed for the missing values. These analyses will consider the results of any losses at follow-up to the extent that they relate to differences in the measured variables (i.e., under the assumption of random missingness).

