### Adverse event reporting and harms {22}

Adverse events, such as unfavorable and undesirable signs, symptoms, abnormal laboratory results, or illnesses temporally associated with the intervention diet, will be collected from the time of randomization until the final 7-month follow-up visit for each participant, whether or not they are considered related to the intervention study. All adverse events will be followed up until their resolution.

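### A randomized participant who starts a weight-loss product on medical advice is excluded from the study, and nothing keeps that person's LDL measured for the promised intention-to-treat analysis (minor, avoidable loss)

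*Protocol article*

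**What the plan says.** Section 11d of the protocol article treats two groups of products. For cortisone, antidiabetic drugs and vitamin or mineral supplements, participants report the need and "their continuation in the study will be evaluated accordingly". For the second group the wording is stricter: "Additionally, the use of products designed for weight loss will not be permitted". The closing sentence then refers back to the products without naming them. A participant who has to start one on a doctor's advice "during the intervention period, they will be excluded from the study".

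Section 14 makes the analysis promise: "Dropouts will be incorporated into the intention-to-treat analysis, including all participants initially randomized". It also plans a per-protocol analysis of those who finish without major deviations.

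Four other sections bear on what happens after a product start:

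- Section 11b: "Participants may discontinue the intervention or withdraw from the study" at their own request or when the investigator sees a health risk. It names both routes but does not say which circumstance leads to which.
- Section 18b: participants who choose to stop early have no further clinical or laboratory assessments.
- Section 22: adverse events "will be collected from the time of randomization until the final 7-month follow-up visit for each participant".
- Section 20c: sensitivity analyses assume that "the missing outcomes are the worst or best possible in the different randomization groups". If the conclusions differ, multiple imputation follows under an assumption of random missingness.

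**The concern.** Exclusion here follows an event after randomization and is exclusion from the study, not only from the diet or the per-protocol set. It therefore ends LDL collection for someone whom the intention-to-treat analysis is meant to include. The person can stay on the list of randomized participants, but only with imputed or bounded values.

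The crossover raises the cost per person, because the metric is the change over each 3-month phase. Exclusion before T1 leaves no change on either diet. Exclusion between T2 and T3 leaves a change on one diet only.

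The reason for the loss may be related to diet or outcome. The diets are isocaloric as prescribed, so weight gain is not expected by design. But no meals are supplied and "Participants will prepare their own meals or eat at a restaurant", so weight can still move. A doctor's decision to start a weight-loss product is then not obviously unrelated to the diet or to LDL.

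The unclear reach of the rule adds to this, because two recruiting sites could apply it differently.

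**Working it through.** **1. The plan's own figure.** Section 14 gives 38 participants (at least 19 per group) for a 10% LDL change at 90% power and alpha 0.05, raised to 25 per group. It states no SD, so 38 cannot be reproduced independently. Solving backwards (two-sided, t-based):

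- 19 per group, two-sample: standardized effect 1.081, SD = 10/1.081 = 9.25 points.
- 38 pairs: standardized effect 0.540, SD = 10/0.540 = 18.5 points.

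Points are percent of baseline LDL. The 9.25 is the SD of one person's change on one diet. It equals the SD of the within-person difference between diets only if the two changes correlate 0.5, since SD(difference) = SD × √(2(1 − r)). I use 9.25 to 18.5 as an assumed range for that difference. The standard error at n = 50 is SD/√50 = 1.31 to 2.62.

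**2. Precision is covered.** The increase from 38 to 50 corresponds to 1 − 38/50 = 24% loss. On the two-sample reading with a normal approximation (SD 9.51), power is 96.1% at 25 per group, 95.4% at 24 and 90.0% at 19. One exclusion is 1/50 = 2% of the trial.

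**3. Number of exclusions, k.** The documents give none. Zero is plausible: BMI is 25.0 to 29.9, the diets are normocaloric, and the phases last 3 months. I show k = 0, 1 and 2 as assumptions. If the rule also covers antidiabetic drugs and supplements, k could be higher.

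**4. Best/worst-case range that section 20c would show.** Set each missing within-person difference to the lowest and then the highest observed value, about ±2.24 SD:

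width = k × (2 × 2.24 × SD)/50

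| k | SD 9.25 | SD 18.5 |
|---|---|---|
| 0 | 0 | 0 |
| 1 | 0.83 | 1.66 |
| 2 | 1.66 | 3.32 |

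Against the 10-point target this is 8% to 17% for one person and 17% to 33% for two. Every dropout adds to the range in the same way. One or two exclusions are 1/12 to 2/12 of what the full allowance of 12 would add.

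**5. Possible selection bias.** Suppose those excluded sit high on a health change that correlates ρ with the LDL difference, and that exclusions occur only in the high-UPF phase. Then

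bias = −k × ρ × SD × z̄/(50 − k)

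where z̄ is their mean standardized position. If they are the very worst-off, z̄ is 2.25 for k = 1 and 2.05 for k = 2. If they are random members of the worse-off half, z̄ is 0.79. For ρ from 0.3 to 0.7:

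| k | Worst-off excluded | Random from worse-off half |
|---|---|---|
| 1 | −0.13 to −0.59 | −0.04 to −0.21 |
| 2 | −0.24 to −1.11 | −0.09 to −0.42 |

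The largest entries are 0.59/2.62 = 0.23 and 1.11/2.62 = 0.42 of a standard error. With ρ = 0 or k = 0 there is no bias. If exclusions occur in both phases, it partly cancels.

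**6. What continued measurement brings in.** If the product or the stopped diet shifts measured LDL by d points, the estimate moves by k × d/50. For d = 5 to 20 (assumed) this is 0.1 to 0.4 for one person and 0.2 to 0.8 for two.

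**The case against.** The strongest reply is that the matter is too small to raise. The event count is assumed and may be zero, and the larger bias figures need several unfavourable conditions at once. The remedy's own shift (0.1 to 0.8) is of similar size to the bias it removes, and exceeds it when those excluded are random members of the worse-off half. This stands: no net gain in bias is shown. What remains is narrower. Measured values allow an analysis with post-start LDL and one without it. Exclusion takes away the first.

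A second reply is that the aim is to isolate food processing, so leaving out LDL affected by a weight-loss product is defensible. That is fair as a choice of estimand, but the planned per-protocol analysis is the place for it. The promised intention-to-treat analysis is a different one.

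Third, section 20c investigates the causes of missing data and, with weight and LDL measured at each visit, random missingness may be tolerable. That mitigates the loss but recovers no value.

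Fourth, the article condenses a fuller protocol. If that document keeps excluded participants under measurement, only the wording here needs correcting. As written, exclusion from the study is a stated rule of conduct, and an analysis plan cannot restore LDL that was never drawn.

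A reader might also infer more than the text supports:

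- That all listed drugs trigger mandatory exclusion. Section 11d first says continuation is evaluated for cortisone, antidiabetic drugs and supplements, so this is one reading of an ambiguous sentence.
- That section 18b forbids measuring these people. It speaks of participants who choose to stop, not of those whom the rule removes.
- That section 11b already provides the milder route. It only mentions stopping the diet and leaving the study side by side.

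**Conclusion.** The point holds as a minor one. Section 11d removes from the study a randomized participant who starts a weight-loss product on medical advice, and on an ambiguous reading one who starts cortisone, an antidiabetic drug or a supplement. No section keeps that person's LDL measured, although section 14 promises an analysis of all randomized. Section 22's adverse-event collection up to the final visit also fits poorly with the rule, because an excluded person would not be expected to reach that visit.

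The size cannot be established from the documents. The illustrative figures rest on an assumed number of exclusions, an assumed SD range, an assumed correlation and exclusions in one phase only. They suggest a small bias, probably toward no difference. A reader might infer that the primary result is in danger or materially biased. Nothing in the documents supports that, and the sample size allowance covers the loss of precision. The reason to act is that the loss is avoidable at little cost.

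**What to change.** **Section 11d.** Replace exclusion from the study with this rule: the diet is stopped or adapted only where medically needed; the product and its start date are recorded; and the participant, with consent, has LDL measured at the remaining scheduled visits among T1 to T3. State which product classes the rule covers.

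**Section 18b.** Align the follow-up sentence, so that stopping the diet does not by itself end clinical and laboratory assessments for those who agree to continue. Otherwise the broader no-follow-up rule stays in place.

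**Analysis.** Use the measured values in the intention-to-treat analysis (treatment-policy estimand). Count the product start as a major deviation in the per-protocol analysis only. Add a sensitivity analysis that sets aside post-start values, including second-period values after a start in the first period.

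**Cost.** Two amended sentences, one added sensitivity analysis, and at most three already scheduled visits per affected participant, with no new assay. The downside is that post-start LDL may partly reflect the product or the stopped diet. The sensitivity analysis shows how much that matters.
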